#### Single-blind randomization and allocation concealment

All patients requiring transabdominal gynaecological surgery will be randomly assigned via computer-generated sequences placed into sealed envelopes to the following two groups: a general anaesthesia group with preoperative RSB (Group PRE); and a general anaesthesia group with postoperative RSB (Group POST). Treatment allocation will be revealed by opening the envelope on the morning of surgery. All of the patients, in addition to the staff involved in postoperative data collection and analyses, will be blinded to the group allocations. The trial will be monitored by an independent data and safety monitoring organization. The group allocations will not be revealed until the final statistical analysis is completed.

### Interventions

#### Before anaesthesia

All patients will be assessed with the PSQI 1 day before the operation [42]. The PSQI differentiates between good sleepers (PSQI global score < 6) and poor sleepers (PSQI global score ≥ 6) with high sensitivity and specificity. The patients will receive routine general anaesthesia and surgery in this study. No additional requirements or preoperative oral analgesics will be permitted. When the patients are in the operating room, standard monitoring will be performed, including evaluations of systolic blood pressure, diastolic blood pressure, heart rate, electrocardiography, blood oxygen saturation and the BIS. After venipuncture, 3 ml of venous blood will be collected for plasma inflammatory cytokine measurements.

#### General anaesthesia

General anaesthesia will be induced as follows: 2 mg/kg propofol given intravenously (IV); 2 mg midazolam given IV; 0.4 μg/kg sufentanil given IV; and 0.2 mg/kg cisatracurium given IV. The patient’s lungs will be ventilated with intermittent positive pressure. The tidal volume will be adjusted to 6–8 ml/kg, and the ventilator rate will be adjusted to maintain end-tidal CO_2_ at 35–45 mmHg. For maintenance of anaesthesia, sevoflurane (Baxter Healthcare of Puerto Rico, Guayama, Puerto Rico) will be used at an end-tidal concentration of 2–2.5 %, and an air-oxygen (FiO_2_: 50 %) mixture will be adjusted for the maintenance of anaesthesia with intraoperative titration of sufentanil given IV, according to a BIS value of 40 to 60, after intubation in both groups. A 0.05 mg/kg dose of additional cisatracurium will be applied if needed. At the end of surgery, the trachea will be extubated after the return of spontaneous respiration and neuromuscular function, and the patient will then be transferred to the PACU. The patients will receive pain relief (visual analogue scale, VAS, score of less than 3) using 5–10 μg titrated sufentanil. Three millilitres of venous blood will be collected for plasma inflammatory cytokine measurements at the PACU.

#### RSB technique

Before surgery (Group PRE) or at the end of surgery (Group POST), a bilateral single-shot RSB will be performed under ultrasound guidance by one anaesthesiologist. The rectus muscle will be imaged with an ultrasound probe in the transverse orientation at the level of the umbilicus. A broadband (5–12 MHz) linear array ultrasound probe (S-Nerve Ultrasound System, Sonosite, Bothell, Washington, USA) will be used with an imaging depth of 4–6 cm. A PAJUNK (PAJUNK, GmbH, Medizintechnologie, Geisingen, Germany) insulated needle (50-mm, 21-gauge) will be introduced a few millimetres from the probe using an in-plane technique at an angle of approximately 45° to the skin. The ultrasound imaging will allow for identification of the rectus muscle and two hyperechoic railway-like lines deep in this muscle (the posterior rectus sheath and peritoneum). Under direct vision, the needle tip will be advanced to the desired position, where 20 ml of 0.5 % ropivacaine hydrochloride will be injected, causing hydrodissection of the rectus muscle away from the posterior rectus sheath. The technique will be repeated on the opposite side. It will be performed by one investigator using a completely aseptic technique.

#### Postoperative analgesia: PCIA

All of the patients, irrespective of the group allocation, will receive PCIA with oxycodone. A PCIA pump (AponZZB-I50, Nantong, China) will be set up with a bolus injection of 2 mg every 5 minutes for a maximum of 10 mg every 4 hours without basal infusion. The PCIA pump will be stopped on the third postoperative day, and postoperative nausea and vomiting will be treated with 5 mg tropisetron given IV (on the ward).

#### Follow-up visits

The patients in this trial will be visited once daily at 24 and 48 hours postoperatively by one of the research personnel. Assessment of sleep quality during the first postoperative night will be performed using the BIS data, and venous blood will be collected.

#### End of participation in the study

Patients will be excluded from the study for the following reasons: (1) refusal to participate; (2) an exclusion criterion identified during the course of the intervention; and/or (3) the occurrence of a severe adverse event.

#### Criteria for removal from the study

During the study, patients found to have the following criteria will be removed from the study: (1) the loss of over 500 ml of blood during surgery; (2) an operation time of longer than 3 hours; (3) a violation of the trial protocol; (4) an unacceptable risk of a serious adverse event; or (5) desire to withdraw from the study.

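### Randomised patients leave the study for events that arise or are judged after allocation, so the analysed groups lose the protection of randomisation

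*Protocol article*

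**What the plan says.** Protocol article, Single-blind randomization and allocation concealment: "Treatment allocation will be revealed by opening the envelope on the morning of surgery". The people listed there as blinded are the patients and the staff who collect and analyse postoperative data.

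Protocol article, Criteria for removal from the study: "patients found to have the following criteria will be removed from the study". The grounds are "the loss of over 500 ml of blood during surgery", "an operation time of longer than 3 hours", "a violation of the trial protocol", "an unacceptable risk of a serious adverse event", and the patient's wish to withdraw.

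Protocol article, End of participation in the study: besides refusal and an exclusion criterion discovered late, patients are excluded for "the occurrence of a severe adverse event". This rule on an event that has happened stands only here. The removal section speaks of the risk of one.

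The RSB technique section places the block before surgery in Group PRE and at its end in Group POST. The Statistical analysis section names no analysis population and says that a full analysis plan will be written separately. Nothing in the article's text says that removed patients are still followed or analysed.

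**The concern.** Randomisation makes the arms comparable at the moment of allocation. A rule that takes patients out afterwards, on grounds that may relate to arm or outcome, replaces the randomised groups with selected ones.

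The wording is removal from the study, not stopping of treatment. Read plainly, it ends collection of the first-bolus time, 24-hour oxycodone consumption, the first-night BIS recording and the 24- and 48-hour cytokine samples. Data not collected cannot be restored at analysis.

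Two things are at stake. One is the validity of the between-arm comparison, in a trial with only 32 patients per group. The other is the completeness of data after a severe event when the arms are compared.

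**Working it through.** **1. Order of events in each arm**

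- Group PRE: envelope opened, block, surgery (blood loss and duration become known), PACU, primary interval starts.
- Group POST: envelope opened, surgery (blood loss and duration become known), block, PACU, primary interval starts.

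Every ground except withdrawal and a late-found exclusion criterion therefore arises or is judged after allocation. The surgical grounds fall on opposite sides of the block in the two arms.

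**2. Who applies the criteria**

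Blood loss and operation time are numeric thresholds. Protocol violation and unacceptable risk need judgement. The theatre team is not listed as blinded, and whoever gives the block must know the arm. The discretionary criteria are therefore the weaker point.

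**3. The plan's own figures**

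The removal rule carries no figure. The Sample size section gives 203.2 ± 21.5 min (PRE) and 258.2 ± 98.7 min (POST), a planned difference of 258.2 − 203.2 = 55.0 min, and 32 per group. The stated formula gives:

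- mean SD (21.5 + 98.7)/2 = 60.1
- ES = 55.0/60.1 = 0.915
- n = 15.7/0.915² + 1 ≈ 19.75, that is 20 per group

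The stated 32 is not reproduced. That is a separate matter, and this point does not rest on it. The section states no allowance for removals. The figure of 32 is taken as given below.

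**4. Possible bias (all removal inputs are assumptions)**

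(a) If k of n patients in one arm are removed, and their intervals lie g minutes below that arm's mean, the mean of those left rises by k·g/(n − k). With k = 3 and n = 32, all in POST:

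- g = 30: 3 × 30/29 = 3.1 min
- g = 60: 3 × 60/29 = 6.2 min
- g = 100: 3 × 100/29 = 10.3 min, which is 10.3/55 = 19% of the planned difference

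(b) Suppose there is no true effect, and a fraction f = 20% in each arm have complicated surgery and intervals shorter by g = 30 to 60 min. If a fraction q of an arm is removed, all from the complicated patients, the arm mean relative to uncomplicated patients is −g(f − q)/(1 − q).

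- Removal 10% v 10%: difference 0
- Removal 5% v 15%: g × (0.15/0.95 − 0.05/0.85) = 0.099g, or 3.0 to 5.9 min
- Removal 0% v 20%: g × 0.20, or 6 to 12 min

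The sign reverses if the heavier removal falls in the other arm.

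**5. Power if patients are lost**

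Welch t test, two-sided α = 0.05, difference 55.0, SE = √[(21.5² + 98.7²)/n] = √(10,203.94/n):

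| n per group | SE (min) | 55.0/SE | Welch df | Power |
|---|---|---|---|---|
| 32 | 17.86 | 3.08 | 33.9 | 84.9% |
| 28 | 19.09 | 2.88 | 29.6 | 79.6% |
| 24 | 20.62 | 2.67 | 25.2 | 72.7% |

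The lower rows correspond to assumed losses of 4 and 8 patients per group.

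**The case against.** The strongest reply is that the harm is hypothetical. Blood loss and operation time are set by the surgery, the Discussion says that one group of gynaecologists will operate by standard procedures, and nothing in the article suggests that block timing changes either. Equal removal gives zero bias in step 4(b), and about 80% power survives the loss of four patients per group. All of this stands. It limits the claim to a lost safeguard and does not remove the claim. The judgement-based criteria are not covered by this reply. Nor is operation time clearly unrelated to outcome: the Discussion's own rationale is that a later block acts longer after surgery, which implies that a long operation uses up block time in PRE and not in POST.

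A second reply is that the separate analysis plan may define an intention-to-treat set. The absence of such a definition in the article is indeed no fault. But a set of that kind would conflict with the removal wording, and it could not supply data that were never collected.

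A reader might also infer more than the documents support:

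- **That safety data vanish.** Adverse events are still reported to the principal investigator, suspected unexpected serious reactions go to the authorities, and an independent data and safety monitoring organization is named. An event that triggers exclusion has been observed and can be counted by arm. Only data after it are at risk.
- **That failed or misplaced blocks are removed as violations.** The article does not class them so.
- **That POST patients are dropped without a block.** The sequence allows this, but the article does not say when removal takes effect.
- **That the type I error is inflated.** Six losses in POST alone (32 v 26) put the pooled t test at 7% to 8%, but six in PRE alone bring it to about 3.5%, and Welch stays near 5%. This is a pooled-variance effect in a chosen scenario, distinct from selection bias.

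**Conclusion.** The point holds as a defect in a stated rule. Followed as written, the protocol compares patients who pass post-allocation filters, and the discretionary filters can be applied by people who know the arm. The protection of randomisation is lost, and data after a severe event may be missing from the between-arm comparison.

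A biased result is not shown. The size of any bias is unknown because the article gives no removal rates. It runs from zero, when removal is equal and unrelated to arm and outcome, to about 10 of the planned 55 minutes under the assumed loss of three POST patients with intervals 100 minutes below average. Neither end is an estimate, and the direction is not fixed. The power loss, from about 85% to 80% or 73%, depends on the pilot SDs and on the assumed losses.

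**What to change.** In the sections on end of participation and on criteria for removal, stop using blood loss, operation time, protocol violation, severe adverse event or risk of a serious one as grounds for leaving follow-up or analysis. Refusal and withdrawal of consent stay as they are. Then:

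1. Analyse every randomised patient in the allocated group for the primary and secondary outcomes.
2. Keep collecting PCIA, sleep and cytokine data unless consent is withdrawn.
3. Use blood loss above 500 ml, surgery beyond 3 hours and protocol violation only to define a per-protocol sensitivity analysis.
4. Tabulate all severe adverse events by allocated arm.

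This concerns follow-up and analysis only and leaves clinical decisions about treatment untouched. The cost is revised wording in the protocol and analysis plan, data collection for a few more patients who are already on the ward, and slightly more heterogeneity from long or complicated operations.

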#### Assessment of safety

The interventional treatment will be administered to patients under standard monitoring in a fully equipped operation room. It is possible that immediate detection of adverse events will occur, in which case they will be treated immediately. However, administration of RSB will be immediately stopped in cases in which the study participant shows significant deterioration. Moreover, the inclusion of each individual patient in the study will be indicated in the electronic hospital information system and hence will be visible to all the physicians and nurses involved in the care of the patient. This visibility will facilitate the reporting of adverse events to the principal investigator. The principal investigator will report suspected unexpected serious adverse reactions to the health authorities.

#### Data collection and management

Trained staff will record all of the data and complete a trial-specific electronic case report form (eCRF). At the time of patient inclusion, patient data on demographic characteristics and history of past illnesses will be collected, including age, height and weight, and diagnosis. Intraoperative data on the patients, including the operation start time, durations of anaesthesia and surgery, blood pressure, heart rate, volume loading, amount of sufentanil consumed, and plasma concentrations of IL-1, IL-6, TNF-α, and IFN-γ, will be collected at the following time points: at baseline (before induction), upon arrival at the PACU, and at 24 and 48 hours postoperatively.

The time of the first PCIA bolus injection and the amount of cumulative PCIA consumption over 24 hours postoperatively will be recorded.

Furthermore, sleep-related baseline data, including the PSQI score for the previous month, will be recorded. Postoperative sleep quality will be measured using the BIS data for the first night after surgery (Fig. 2).

**Fig. 2 Fig2:**
[figure not shown]
The trial procedures flow sheet. *BIS* bispectral index, *PACU* post-anaesthesia care unit, *PCIA* patient-controlled intravenous analgesia, *PSQI* Pittsburgh Sleep Quality Index, *RSB* rectus sheath block, *VAS* Visual Analogue Scale

#### Sample size

Sample size was calculated on the basis of the average (mean ± standard deviation (SD)) of the interval between leaving the PACU and their receipt of the first PCIA bolus injection on the first postoperative night calculated in the pilot study (Group PRE: 203.2 ± 21.5 minutes; and Group POST: 258.2 ± 98.7 minutes). The formula for determining sample size [43] was *n* = 15.7/*ES*^2^ + 1, where *ES* is the effect size, defined as the difference between the groups divided by the mean of the SD between the groups, with *α* = 0.05 and power = 0.8. The study is adequately powered, with *n* = 32 for each group.

#### Statistical analysis

Statistical analysis will be performed using SPSS software, version 18 for Windows (SPSS, Inc., Chicago, IL, USA). A fully specified statistical analysis protocol will be written in an independent manner. Continuous data will be described as the mean (SD or median (25 and 75 % percentiles) and will be analysed with the independent *t* test or the Mann-Whitney *U* test, respectively. Categorical data will be described as a frequency or percentage and will be analysed by the chi-square test. Repeated analysis of variance (ANOVA) will be used to determine cytokine levels within and between the groups. Before statistical testing, each continuous variable will be analysed to determine whether it has a normal distribution using the Kolmogorov-Smirnov test. Nonparametric data will be assessed using Kruskal-Wallis ANOVA or the Mann-Whitney *U* test as appropriate.

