## Methods/Design

### Study design and outcomes

This study is a prospective, randomised, controlled (randomised, parallel group, concealed allocation), single-blinded trial. All patients undergoing transabdominal gynaecological surgery will be randomised 1:1 to the treatment intervention with RSB preoperatively or postoperatively. The objective of the trial is to evaluate the postoperative pain, sleep quality and changes in cytokine levels of patients undergoing gynaecological surgery with RSB performed preoperatively versus postoperatively.

The primary objective is to compare the interval between leaving the post-anaesthesia care unit (PACU) and receiving the first PCIA bolus injection on the first postoperative night between patients who receive preoperative RSB and those who receive postoperative RSB. The secondary objectives will be to compare the following: (1) cumulative oxycodone consumption at 24 hours after surgery between patients who receive preoperative versus postoperative RSB; (2) postoperative sleep quality, which will be measured using a bispectral index (BIS)-Vista monitor during the first night after surgery [40, 41]; and (3) cytokine levels (interleukin-6 (IL-6), tumour necrosis factor-α (TNF-α), IL-1 and interferon-γ (IFN-γ)), which will be compared during the operation and at 24 and 48 hours postoperatively.

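### Repeated ANOVA for cytokines names no baseline adjustment although a pre-induction sample is collected; adjusting gains precision at almost no cost, by an amount that depends on the correlation

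*Protocol article*

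**What the plan says.** - **Method.** Under Statistical analysis, the sentence on cytokines reads: "Repeated analysis of variance (ANOVA) will be used to determine cytokine levels within and between the groups". It does not say which samples are responses, whether any is a covariate, or which test (group main effect or group-by-time) answers the question of PRE versus POST.
- **Samples.** Data collection and management lists the cytokine times as "at baseline (before induction), upon arrival at the PACU, and at 24 and 48 hours postoperatively". The section Before anaesthesia confirms the first draw: "After venipuncture, 3 ml of venous blood will be collected for plasma inflammatory cytokine measurements".
- **Objective.** Study design and outcomes describes the cytokine levels as ones "which will be compared during the operation and at 24 and 48 hours postoperatively". Baseline is not among these times, and an intraoperative time is.
- **Fallback.** The Statistical analysis section says that "each continuous variable will be analysed to determine whether it has a normal distribution using the Kolmogorov-Smirnov test", and then that "Nonparametric data will be assessed using Kruskal-Wallis ANOVA" or the Mann-Whitney test, as suits the case. This sentence covers all variables and does not single out cytokines.
- **Further plan.** The same section announces: "A fully specified statistical analysis protocol will be written in an independent manner".

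**The concern.** The pre-induction sample precedes anaesthesia and the block in both arms, so randomisation makes the arms equal there in expectation. Its value to the group comparison is as a covariate that explains differences between patients. The named method, taken as written, does not use it that way.

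The natural model for a comparison within and between groups over the four listed samples has four response levels, and its group main effect averages in one level where no difference can exist. If the three times in the objective are taken instead, the baseline sample plays no part.

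The Background hypothesises that the postoperative block will not lower cytokine levels. A needlessly imprecise comparison therefore leans towards the expected conclusion, because a missed difference would be read as confirmation.

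Two smaller matters sit beside this. No paired rank method is named for repeated samples. And the objective names a comparison during the operation for which no intraoperative draw is listed.

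**Working it through.** **Plan's own figure.** There is none for cytokines. The sample size section, with "0.05 and power = 0.8", concerns the primary outcome only. Its 32 per group is taken here as given.

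**Inputs.** From the article: two arms at 1:1, 32 per arm, one pre-induction and three later samples. Assumed: equal variances (set to 1), a common correlation r between any two samples, and a constant group difference d at the three later times. The article gives neither r nor d, so r runs over 0.3, 0.5 and 0.7.

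**Variance of each estimate of d (common factor 2/n omitted).**
- Group main effect with baseline as a level: the four-sample mean differs by 0.75d and has variance (1+3r)/4. Rescaled to d, the variance is [(1+3r)/4]/0.5625.
- Change contrast (mean of the three later samples minus baseline): (1+2r)/3 + 1 − 2r = 4(1−r)/3.
- Post-baseline mean only: (1+2r)/3.
- Post-baseline mean adjusted for baseline: (1+2r)/3 − r² = (1−r)(1+3r)/3.

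| r | Main effect | Change | Post only | Adjusted |
|---|---|---|---|---|
| 0.3 | 0.844 | 0.933 | 0.533 | 0.443 |
| 0.5 | 1.111 | 0.667 | 0.667 | 0.417 |
| 0.7 | 1.378 | 0.400 | 0.800 | 0.310 |

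**Information gain from adjustment (other variance divided by adjusted variance).**

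| Comparator | Formula | r = 0.3 | r = 0.5 | r = 0.7 |
|---|---|---|---|---|
| Main effect, baseline as a level | 4/[3(1−r)] | 1.90 | 2.67 | 4.44 |
| Group-by-time change contrast | 4/(1+3r) | 2.11 | 1.60 | 1.29 |
| Post-baseline only | (1+2r)/[(1−r)(1+3r)] | 1.20 | 1.60 | 2.58 |

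**If baseline predicts poorly.** With a baseline-to-later correlation of 0.1 to 0.3 and a correlation of 0.5 to 0.7 among later samples, the gains are 1.24 to 1.70, 1.69 to 2.23, and 1.01 to 1.16 in the same order.

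**Power.** Simulated at 32 per arm, d = 0.5 SD (assumed), 4,000 runs. The group-by-time test here is the usual F test on 3 degrees of freedom.

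| r | Main effect | Group-by-time | Post only | Adjusted |
|---|---|---|---|---|
| 0.3 | 56% | 38% | 76% | 83% |
| 0.5 | 46% | 50% | 66% | 85% |
| 0.7 | 37% | 76% | 58% | 94% |

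With no true difference, all four rejected about 5% of the time.

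**Rank methods.** With two arms, Kruskal-Wallis between groups is equivalent to Mann-Whitney, so a separate use for it would be across time points. Simulated there on 32 patients with four correlated samples and no change over time, it rejected in about 1.3%, under 0.5% and almost 0% of runs at r = 0.3, 0.5 and 0.7. Friedman stayed near 5%. With a 0.5 SD shift at one time and r = 0.7, power was about 31% against 91%.

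**Sampling times.** The listed draws are before induction, PACU arrival, 24 h and 48 h. None is intraoperative.

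**The case against.** The strongest reply is that the article never says baseline is an outcome level. The sampling list is a data-collection list and not a model, and the objective leaves baseline out of the compared times. This stands: a reader may infer a four-level ANOVA, but the article does not state one. The point survives because adjustment is more informative under either reading.

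A second reply is that an analysis protocol is announced and may settle covariates. That is fair for details such as transformation and missing samples. But the article already names the model, and a better use of a sample already planned is a recommendation about that choice. Repeated ANOVA is not invalid, since its error rate held.

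Further inferences should be resisted:
- **That adjustment always at least doubles the information.** Against the main effect this needs r of at least 1/3, against the change contrast r of at most 1/3, and against a post-only analysis r of about 0.6 or more.
- **That the objective loses most of its power.** Taking the better of the two ANOVA tests at each r, power is 56% v 83%, 50% v 85% and 76% v 94%, so roughly 60% to 80% of it is kept. The group-by-time test also removes stable differences between patients.
- **That the nonparametric route is invalid for PRE versus POST.** Mann-Whitney between arms at a single time is valid. The Kruskal-Wallis problem touches only change over time within patients, and the fallback sentence does not mention cytokines.
- **That many patients would drop out of the ANOVA through missing samples.** The article gives no missingness rate on which to base this.

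**Conclusion.** The point holds as an efficiency recommendation on a secondary objective. The named cytokine analysis makes no stated use of the pre-induction sample as a covariate. Under equal variances, a common correlation of 0.3 to 0.7 and a constant later difference, adjustment was the more informative choice against every plausible reading of the plan, by a factor between 1.2 and 4.4. With a weakly predictive baseline, the gain over a post-only analysis can all but vanish (1.01). The size is therefore conditional on a correlation that the article does not give.

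That baseline enters as a response, with dilution to 3/4, is one reading and not a stated fact. The unsuitability of Kruskal-Wallis is confined to comparisons across time within patients. The mismatch between the objective's intraoperative comparison and the listed draws needs no assumption. None of this bears on the primary outcome.

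**What to change.** - Analyse the PACU-arrival, 24 h and 48 h values, on a log scale if skewed, in a repeated-measures or mixed model with baseline as covariate and group, time and group-by-time as fixed effects. State which term answers PRE versus POST.
- If a rank method is wanted for change over time within patients, name a paired one such as Friedman in place of Kruskal-Wallis. Mann-Whitney between arms at a single time can stay.
- Reconcile the objective's comparison during the operation with the four sampling times listed.

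The cost is wording in the article's analysis section or the announced analysis protocol, settled before unblinding. No extra blood is drawn. The covariate uses one of 62 error degrees of freedom in the between-patient comparison (64 patients less two arm means) and needs a recorded baseline value.

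### A normality test on the outcome data chooses the primary test and so leaves the estimand open; with the pilot SDs this can raise type I error and can cost power

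*Protocol article*

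**What the plan says.** The protocol's Statistical analysis section states that "each continuous variable will be analysed to determine whether it has a normal distribution using the Kolmogorov-Smirnov test". Continuous data "will be analysed with the independent" t test or the Mann-Whitney U test, and data judged non-normal go to the rank tests. The primary endpoint, the interval from leaving the PACU to the first PCIA bolus, is a continuous variable and no separate test is fixed for it.

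The section does not say whether the Kolmogorov-Smirnov (KS) test is run on both arms pooled or by arm, at what level, or with the Lilliefors correction for estimated parameters. It does not say whether the t test allows unequal variances. It announces a separate full analysis plan, which is not shown.

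The Sample size section works on means. It takes the primary interval as "calculated in the pilot study" ("Group PRE: 203.2 ± 21.5 minutes; and Group POST: 258.2 ± 98.7 minutes"), uses an effect size "defined as the difference between the groups divided by the mean of the SD between the groups", sets α at "0.05 and power = 0.8", and arrives at "32 for each group". Under Study design and outcomes, patients "will be randomised 1:1 to the treatment intervention with RSB preoperatively or postoperatively".

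**The concern.** This is a stated rule, not a detail left to the analysis plan, and a plan that follows it inherits the problem. The two candidate tests answer different questions. The t test concerns the difference in mean minutes. Mann-Whitney concerns P(POST > PRE), the probability that a random POST patient waits longer than a random PRE patient. Which of these is the primary comparison would be known only after the outcome data are seen.

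The protocol's own pilot figures make this more than a formality. KS looks at shape and not at variance, yet an SD ratio of 4.6 affects it: two normal arms with very different SDs, pooled, form a mixture that is not normal. Unequal spread can then send the analysis to Mann-Whitney, which is not a valid test of a location difference under such spread. At stake are the stated α of 0.05 and power of 0.8, both computed for a difference in means.

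**Working it through.** **Inputs from the Sample size section.** PRE 203.2 (SD 21.5) and POST 258.2 (SD 98.7) minutes; 32 per arm. Difference 258.2 − 203.2 = 55.0. SD ratio 98.7/21.5 = 4.59.

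**Step 1, the plan's own figure.** Mean SD = (21.5 + 98.7)/2 = 60.1. ES = 55.0/60.1 = 0.915. n = 15.7/0.915² + 1 = 19.75, so 20 per group. The stated 32 is not reproduced. That is a separate matter; what counts here is that the calculation is for a mean difference.

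**Step 2, Welch at 32 per arm.** SE² = 21.5²/32 + 98.7²/32 = 14.45 + 304.43 = 318.87, so SE = 17.86. The standardised difference is 55.0/17.86 = 3.08. Degrees of freedom = 318.87² / [(14.45² + 304.43²)/31] = 33.9. Noncentral t power is 84.9%. The fixed test meets the 80% target.

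**Step 3, the two-stage rule by simulation.** Assumptions: KS at 5%; t test if not rejected, Mann-Whitney if rejected; pilot SDs; 32 per arm. There were 100,000 trials for the first two shapes and 20,000 for lognormal. Gamma means a normal PRE arm with a gamma POST arm; gamma in both arms gives nearly the same result. Shapes and KS variants are assumptions because the protocol gives neither.

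Type I error for a mean difference (equal means, unequal SDs), %:

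| Procedure | Normal | Gamma | Lognormal |
|---|---|---|---|
| KS pooled, Lilliefors | 7.8 | 14.9 | about 22 |
| KS pooled, uncorrected | 5.3 | 8.7 | between |
| KS by arm, Lilliefors | 6.1 | 12.2 | between |
| KS by arm, uncorrected | 5.3 | 6.1 | about 8 |
| Welch alone | 5.0 | 5.4 | 6.5 |

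Power at +55 minutes, %:

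| Procedure | Normal | Gamma | Lognormal |
|---|---|---|---|
| KS pooled, Lilliefors | 81.2 | 69.9 | 69.0 |
| KS pooled, uncorrected | 80.9 | 72.3 | 71.7 |
| KS by arm, Lilliefors | 85.3 | 83.4 | 81.0 |
| KS by arm, uncorrected | 85.8 | 89.0 | 90.6 |
| Welch alone | 85.0 | 88.3 | 90.1 |

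**Step 4, where the effect comes from.** With both arms exactly normal, uncorrected pooled KS rejects in 26% of trials at equal means and 58% at +55 minutes; with Lilliefors the figures are 94% and 99%. The variance ratio itself therefore drives the choice. Mann-Whitney alone has type I error 8.1% (normal) and 16.0% (gamma). Uncorrected KS by arm rejects in at most about 3% of trials for these shapes, so it nearly always leaves the plain t test.

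**Step 5, no difference of any kind.** When both arms share one distribution, the two-stage rule rejects in 4.8-5.5% of trials over the shapes and variants above.

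**Step 6, unequal arms.** At 32/32 the equal-variance and Welch standard errors coincide, and the t test rejects in 5.3% (normal). The section on criteria for removal takes patients out after randomisation, so final arms may differ in size. With 32 PRE and 28 POST, pooled variance = (31 × 462.25 + 27 × 9741.69)/58 = 4782. Assumed SE² = 4782 × (1/32 + 1/28) = 320.2; true SE² = 462.25/32 + 9741.69/28 = 362.4. The assumed SE is √(320.2/362.4) = 0.94 of the true one. Simulated type I error is about 7%, and about 8% at 32/26; Welch stays at 5.0%. The opposite imbalance (26 PRE, 32 POST) makes the t test conservative, at 3.3%.

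**The case against.** A reader might infer that the rule, as written, inflates type I error and loses power outright. The documents do not support that, for four reasons.

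- **The KS variant is open.** Uncorrected KS by arm shows almost no harm with normal or gamma data and no power loss against Welch for any of the three shapes. The unseen analysis plan may settle the variant.
- **The null is a particular one.** Inflation needs equal means with very unequal SDs. If timing changes nothing, so that both arms share one distribution, error stays near 5%.
- **Part of the excess is a different question.** With skewed data of equal mean and unequal SD, P(POST > PRE) is not one half, so many Mann-Whitney rejections are correct for its own hypothesis. They are errors only as statements about means. Under normality P(POST > PRE) is one half, so the 8.1% there is a true loss of level.
- **The planned power is not clearly broken.** With normal data it stays at 80% or more under every variant; it drops below 80% only with skewed data and pooled KS.

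It is also fair that 1:1 allocation with 32 per arm protects the equal-variance t test, and that the pilot's size and data shape are not given.

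All of this limits the size of the effect. It leaves the main point untouched: the protocol lets the data pick the primary test and estimand, and the harmless variants are harmless because the pre-test then almost never acts.

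**Conclusion.** The point holds in a conditional form. The rule leaves the primary test and its estimand open until the data are seen, although the trial is sized on a mean difference. Given the pilot SDs, it can raise type I error for that difference: about 5-8% (normal), 6-15% (gamma) and 8-22% (lognormal), against about 5-6.5% for Welch. It can cost power, from nothing to about 4 points with normal data and up to about 20 points with skewed data; the low end comes from pooled KS. If the wider POST arm ends up the smaller one, the equal-variance t test adds an excess of its own (about 7-8% at 32/28 to 32/26).

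These figures rest on the pilot SDs being about right, on the assumed shapes and on the KS variants tried. The open choice of test and estimand rests on none of them. This should be changed, but it does not threaten the trial.

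**What to change.** Drop the normality pre-test for the primary outcome. State in advance that the primary analysis is Welch's unequal-variance t test on the interval in minutes, reported as the POST minus PRE mean difference with a 95% CI. This matches the scale of the sample size and needs no variance check. Keep Mann-Whitney as a labelled sensitivity analysis, described as addressing P(POST > PRE).

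The cost is a change of wording in the protocol and in the analysis plan it announces; SPSS already prints the unequal-variance result. The one statistical drawback is that Welch runs slightly above 5% with strongly skewed data (6.5% in the lognormal case), which is still below the two-stage rule under every variant tried for that shape.
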